**1. Is your project research?**

☒ Yes ☐ No

**2. Select one category from the list below:**

- ☐ Clinical trial of an investigational medicinal product
- ☐ Clinical investigation or other study of a medical device
- ☐ Combined trial of an investigational medicinal product and an investigational medical device
- ☐ Other clinical trial to study a novel intervention or randomised clinical trial to compare interventions in clinical practice
- ☒ Basic science study involving procedures with human participants
- ☐ Study administering questionnaires/interviews for quantitative analysis, or using mixed quantitative/qualitative methodology
- ☐ Study involving qualitative methods only
- ☐ Study limited to working with human tissue samples (or other human biological samples) and data (specific project only)
- ☐ Study limited to working with data (specific project only)
- ☐ Research tissue bank
- ☐ Research database

**If your work does not fit any of these categories, select the option below:**

☐ Other study

**2a. Will the study involve the use of any medical device without a UKCA/CE UKNI/CE Mark, or a UKCA/CE UKNI/CE marked device which has been modified or will be used outside its intended purposes?**

☐ Yes ☒ No

**2b. Please answer the following question(s):**

a) Does the study involve the use of any ionising radiation?

☒ Yes ☐ No

• Does the study involve exposure to radioactive materials?

☐ Yes ☒ No

b) Will you be taking new human tissue samples (or other human biological samples)?

☒ Yes ☐ No

c) Will you be using existing human tissue samples (or other human biological samples)?

☐ Yes ☒ No

d) Will the study involve any other clinical procedures with participants (e.g. MRI, ultrasound, physical examination)?

☒ Yes ☐ No

**3. In which countries of the UK will the research sites be located?(Tick all that apply)**

- ☒ England  
☐ Scotland  
☐ Wales  
☐ Northern Ireland

**3a. In which country of the UK will the lead NHS R&D office be located:**

- ☐ England  
☐ Scotland  
☐ Wales  
☐ Northern Ireland  
☒ This study does not involve the NHS

**4. Which applications do you require?**

- ☐ NHS/HSC Research and Development offices  
☐ Social Care Research Ethics Committee  
☒ Research Ethics Committee  
☐ Confidentiality Advisory Group (CAG)  
☐ Her Majesty's Prison and Probation Service (HMPPS)

**5. Will any research sites in this study be NHS organisations?**

☐ Yes ☒ No

**6. Do you plan to include any participants who are children?**

☐ Yes ☒ No

**7. Do you plan at any stage of the project to undertake intrusive research involving adults lacking capacity to consent for themselves?**

☐ Yes ☒ No

*Answer Yes if you plan to recruit living participants aged 16 or over who lack capacity, or to retain them in the study following loss of capacity. Intrusive research means any research with the living requiring consent in law. This includes use of identifiable tissue samples or personal information, except where application is being made to the Confidentiality Advisory Group to set aside the common law duty of confidentiality in England and Wales. Please consult the guidance notes for further information on the legal frameworks for research involving adults lacking capacity in the UK.*

**8. Do you plan to include any participants who are prisoners or young offenders in the custody of HM Prison Service or who are offenders supervised by the probation service in England or Wales?**

☐ Yes ☒ No

**9. Is the study or any part of it being undertaken as an educational project?**

☒ Yes ☐ No

Please describe briefly the involvement of the student(s):

The primary researcher is a second year PhD student at Durham University. She will be responsible for participant recruitment, all data collection and storage, under the supervision of [name] and [name].

**9a. Is the project being undertaken in part fulfilment of a PhD or other doctorate?**

☒ Yes ☐ No

**10. Will this research be financially supported by the United States Department of Health and Human Services or any of its divisions, agencies or programs?**

☐ Yes ☒ No

**11. Will identifiable patient data be accessed outside the care team without prior consent at any stage of the project (including identification of potential participants)?**

☐ Yes ☒ No

**Integrated Research Application System****Application Form for Basic science study involving procedures with human participants**[figure not shown]**Application to NHS/HSC Research Ethics Committee**

The Chief Investigator should complete this form. Guidance on the questions is available wherever you see this symbol displayed. We recommend reading the guidance first. The complete guidance and a glossary are available by selecting [Help](#).

Please define any terms or acronyms that might not be familiar to lay reviewers of the application.

**Short title and version number:** (maximum 70 characters - this will be inserted as header on all forms)  
Sex Differences in Muscle Damage: Exercise Load & Protein Feeding (v1)

*Please complete these details after you have booked the REC application for review.*

**A2-2. Who will act as Chief Investigator for this study?**

- ☒ Student
- ☐ Academic supervisor
- ☐ Other

**Registry reference number(s):**

*The UK Policy Framework for Health and Social Care Research sets out the principle of making information about research publicly available. Furthermore: Article 19 of the World Medical Association Declaration of Helsinki adopted in 2008 states that "every clinical trial must be registered on a publicly accessible database before recruitment of the*

*first subject"; and the International Committee of Medical Journal Editors (ICMJE) will consider a clinical trial for publication only if it has been registered in an appropriate registry. Please see guidance for more information.*

International Standard Randomised Controlled Trial Number (ISRCTN):

ClinicalTrials.gov Identifier (NCT number):

**Additional reference number(s):**

| Ref.Number | Description | Reference Number |
|------------|-------------|------------------|
|------------|-------------|------------------|

**A5-2. Is this application linked to a previous study or another current application?**

☐ Yes ☒ No

*Please give brief details and reference numbers.*

**2. OVERVIEW OF THE RESEARCH**

*To provide all the information required by review bodies and research information systems, we ask a number of specific questions. This section invites you to give an overview using language comprehensible to lay reviewers and members of the public. Please read the guidance notes for advice on this section.*

**A6-1. Summary of the study.** *Please provide a brief summary of the research (maximum 300 words) using language easily understood by lay reviewers and members of the public. Where the research is reviewed by a REC within the UK Health Departments' Research Ethics Service, this summary will be published on the Health Research Authority (HRA) website following the ethical review. Please refer to the question specific guidance for this question.*

Unaccustomed resistance exercise can cause damage to muscle fibres that may consequently lead to muscle soreness, loss of strength, and reduced flexibility for several days following the exercise bout. These impairments prolong recovery time and likely impact exercise performance, which over time, may limit the gains in muscle mass and strength associated with resistance training. Therefore, establishing strategies to limit exercise-induced muscle damage will be advantageous to exercising individuals. This research will investigate the impact of exercise intensity in both sexes (part A) and dietary protein feeding (part B) as potential strategies for reducing muscle damage.

For part A of the research, young, healthy males and females (n = 40) will be recruited. Participants will perform a single bout of leg-based resistance exercise using either heavy or lighter weights. Muscle damage will be assessed before, immediately after, and in 24-hour intervals after the exercise through indirect blood markers (from blood samples), self-perceived muscle soreness (via pressure algometry), and muscle function (strength and flexibility). Muscle damage will be compared between sexes and exercise loads, and related to total lean body mass, as determined by dual energy X-ray absorptiometry (DXA) at baseline.

For part B of the research, young, healthy females (n = 22) will be recruited. Participants will perform a single bout of high-intensity leg-based resistance exercise. Before the exercise, and every 4 hours afterwards for 3 days participants will consume either 20 g of milk protein or a carbohydrate-based placebo. Previous research has shown that milk protein effectively reduces muscle soreness, helps maintain strength, and lowers the concentration of damage and inflammatory biomarkers in males, but this has not yet been investigated in untrained females. Muscle damage will be assessed as per part A and compared between the protein and placebo groups and related to baseline body composition, as determined by DXA.

**A6-2. Summary of main issues.** *Please summarise the main ethical, legal, or management issues arising from your study and say how you have addressed them.*

*Not all studies raise significant issues. Some studies may have straightforward ethical or other issues that can be identified and managed routinely. Others may present significant issues requiring further consideration by a REC, R&D office or other review body (as appropriate to the issue). Studies that present a minimal risk to participants may raise complex organisational or legal issues. You should try to consider all the types of issues that the different reviewers may need to consider.*

Collection of blood samples may cause discomfort, minor bruising, and carries a risk of infection - blood samples will be collected by a trained phlebotomist wearing the correct personal protective equipment (e.g. disposable gloves,

laboratory coat). All surfaces (e.g. chair, tables) will be cleaned before and after use and the researcher will practice hand washing prior to touching any equipment.

Performing the resistance exercise may cause musculoskeletal injury - A readiness to exercise questionnaire will be completed prior to testing and participants will not be eligible to participate if they have a current or previous (past 3 months) musculoskeletal injury. Participants will be demonstrated correct lifting technique; perform an appropriate warm-up; and be supervised at all times.

Performing the Pressure-Pain Threshold test with a pressure algometer may cause discomfort and minor bruising - The participant will be instructed to indicate when the pressure applied with the algometer becomes painful, at which point, the pressure will be released. The test will be performed on alternate legs to reduce bruising of the same site and participants will be advised to treat any bruising with rest, ice, compression, and elevation.

Assessing body composition by dual energy X-ray absorptiometry exposes the participant to ionising radiation. The effective dose received per scan is minimal and considered safe at 0.002 mSv, which is the equivalent of a few days of natural background radiation in the UK. Multiple DXA scans are considered safe to both the participant and researcher.

There is a risk of spreading or being infected with Covid-19. The laboratory has a maximum occupancy that will be adhered to; a 2 metre distance will be maintained where possible; where close contact is required e.g. when taking blood samples, performing the pressure-pain threshold test, and measuring leg circumference, a face covering will be worn by both the researcher and participant and the researcher will wear disposable gloves; all surfaces including the exercise equipment will be cleaned before and after use with the correct cleaning solution; frequent hand-washing will be performed; and if either a participant or the researcher develops Covid-19 symptoms they will be instructed not to attend the laboratory and to self-isolate in line with government guidance.

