Visit three will occur three weeks later. In between visits two and three, participants will be asked to record their habitual diet and activity for three days, which will be used to assess any between-group differences. For each subsequent assessment day, participants will be prescribed a standardised breakfast to consume at home 3 hours prior to attending the laboratory. Otherwise, participants will be instructed to consume their habitual diet and, during each laboratory visit, a 24-hour dietary recall will be conducted to assess any changes in dietary intake. Participants will be instructed to abstain from the use of non-steroidal anti-inflammatory drugs, strenuous exercise, engagement in massage or cryotherapy, and the consumption of alcohol, protein supplements, vitamin and mineral supplements, and ergogenic aids during the study period.

Upon arriving at the laboratory for the third visit (pre), a trained phlebotomist will collect a venous blood sample in three vacutainers; one containing a serum separator (8.5 mL); and two containing no reagent (10 mL) (28.5 mL total). Following blood collection, the participants' limb circumference of the thigh will be measured with a standard measuring tape and their limb range of motion will be assessed with a goniometer. Muscle soreness will be measured by use of a visual analogue scale (VAS) questionnaire while performing a standard bodyweight squat, and the pressure-pain threshold (PPT) test using a standard pressure algometer. Participants will then perform a single bout of resistance exercise at their allocated load intensity, firstly on the leg press and secondly, on the leg extension, separated by five-minutes rest. The exercise protocol will consist of a warm-up set (10 repetitions at 50% of the participants pre-established 1RM), followed by three sets performed to volitional failure (when a full repetition can no longer be completed) at either 30% or 80% 1RM. Two-minutes of rest will be awarded between each set of exercise and the participants will be verbally encouraged throughout.

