Immediately following the exercise bout (post), another venous blood sample will be taken (3 x 8.5-10 mL) and the measures of limb circumference, range of motion, and muscle soreness will be repeated. Then, participants will be provided a dairy yoghurt containing 20 g of milk protein to stimulate muscle repair and growth. These four measures (excluding protein consumption) will be repeated during the morning of visits four (+24 h), five (+48 h), six (+72 h), and seven (+168 h). Also, during visits six and seven, the 1RM strength test will be repeated on the leg press and leg extension. Over the experimental period, a total of 171 mL of blood will be collected from each participant. This is the equivalent of ~34 teaspoons and is a common amount obtained during exercise physiology research. The blood samples will be used to analyse serum concentrations of creatine kinase, myoglobin (markers of muscle damage), C-reactive protein, and interleukin-6 (markers of inflammation).

**OBJECTIVE 2/PART B:** This study will employ a randomised parallel groups design, for which 22 healthy females aged 18-35 years will be recruited. Prior to the first laboratory visit, prospective participants will have the opportunity to ask questions and gain further information about the study via a video/phone call with the lead researcher. If willing to participate, participants will be asked to electronically sign a consent form. Participants will be asked to record their menstrual cycle and inform the lead researcher at the onset of menses – this information will be used to arrange the time of the baseline assessments, as all measures will be conducted during the late follicular phase of the menstrual cycle.

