|                                                                                              |    |   |         |                                                                                                                       |
|----------------------------------------------------------------------------------------------|----|---|---------|-----------------------------------------------------------------------------------------------------------------------|
|                                                                                              |    |   | mins    | Human Performance Laboratory, Durham University                                                                       |
| Measurement of muscle soreness by pressure algometry and visual analogue scale questionnaire | 12 | 0 | 15 mins | [name];
Human Performance Laboratory, Durham University                                                     |
| Measurement of leg range of motion by goniometry                                             | 12 | 0 | 5 mins  | [name];
Human Performance Laboratory, Durham University                                                     |
| Measurement of leg circumference by standard tape measure                                    | 12 | 0 | 5 mins  | [name];
Human Performance Laboratory, Durham University                                                     |
| Completion of a leg-based resistance exercise protocol                                       | 2  | 0 | 30 mins | [name];
Human Performance Laboratory, Durham University                                                     |
| Ingestion of milk protein (yoghurt) or carbohydrate-based placebo (Part B only)              | 17 | 5 | 5 mins  | [name] will provide the milk protein for the participants to consume either at the laboratory or at their home |

**A19. Give details of any clinical intervention(s) or procedure(s) to be received by participants as part of the research protocol.** *These include uses of medicinal products or devices, other medical treatments or assessments, mental health interventions, imaging investigations and taking samples of human biological material. Include procedures which might be received as routine clinical care outside of the research.*

Please complete the columns for each intervention/procedure as follows:

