**A57. What is the primary outcome measure for the study?**

Exercise-induced changes in markers of muscle damage

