**A61. Will participants be allocated to groups at random?**

☒ Yes ☐ No

*If yes, please give details of the intended method of randomisation:*

With each eligible participant identified, a coin will be tossed to decide which group they go into.

**A62. Please describe the methods of analysis (statistical or other appropriate methods, e.g. for qualitative research) by which the data will be evaluated to meet the study objectives.**

PART A: The Shapiro Wilk test will be used to assess the distribution of the data and to ensure no assumptions for statistical models are violated. Any data that violate the assumptions will be logarithmically transformed before statistical analysis. A two-way mixed design analysis of variance (ANOVA) will be used to analyse each muscle damage marker between exercise conditions and within time points. A two-way between-subjects ANOVA will be used to analyse each muscle damage marker between exercise conditions and between sexes. Independent t tests with Bonferroni corrections will be used to compare time-points between exercise conditions for all measures. Paired t tests will be used to detect any significant within-group changes between time points.

PART B: The Shapiro Wilk test will be used to assess the distribution of the data and to ensure no assumptions for statistical models are violated. Any data that violate the assumptions will be logarithmically transformed before statistical analysis. A two-way mixed design ANOVA will be used to analyse each muscle damage marker between dietary conditions (protein or placebo) and within time points. Independent t tests with Bonferroni corrections will be used to compare time-points between dietary conditions for all measures. Paired t tests will be used to detect any significant within-group changes between time points.

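### If the pain-threshold test alternates legs from one occasion to the next, three of five changes from baseline compare different legs, and no starting leg is set or balanced

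*Protocol*

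**What the plan says.** The leg rule appears twice, in the same words, in the summary of main issues (A6-2) and under risks and burdens (A22): "The test will be performed on alternate legs to reduce bruising of the same site".

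The schedule is in A13 and is the same for Parts A and B. At visit three, before exercise, soreness is measured by a visual analogue scale (VAS) and by "the pressure-pain threshold (PPT) test using a standard pressure algometer". Immediately after exercise "the measures of limb circumference, range of motion, and muscle soreness will be repeated". The measures then "will be repeated during the morning of visits four (+24 h), five (+48 h), six (+72 h), and seven (+168 h"). The table in A18 lists "Measurement of muscle soreness by pressure algometry and visual analogue scale questionnaire" 12 times over the two parts.

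The lay summary (A6-1) counts "self-perceived muscle soreness (via pressure algometry") among the damage measures. The primary outcome in A57 is "Exercise-induced changes in markers of muscle damage". A62 plans a mixed ANOVA of each damage marker by group and time, independent t tests between groups at each time point, and this for changes within groups: "Paired t tests will be used to detect any significant within-group changes between time points".

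The protocol does not name a starting leg, randomise or balance it, take a baseline on both legs, or mention leg in the analysis.

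**The concern.** A change from baseline in pain threshold is interpretable when both readings come from the same site. If the leg switches at each occasion, leg is fully determined by time point within a participant, and there is only one pre-exercise reading to compare with.

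Two things could go wrong. First, if participants tend to start on the same side, any average left-right difference in threshold is added to the time course and reads as soreness or recovery. Second, even with no average difference, a change taken across legs carries each person's own leg-to-leg difference as extra error. Part A has 10 participants per sex-by-load cell and Part B about 11 per group, so the extra error could matter.

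An analysis plan written later could not repair this. If everyone starts on the same leg, a leg term is a linear combination of the six time levels and cannot be estimated separately. If the leg is not recorded, it cannot be modelled at all.

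**Working it through.** **Step 1. Number of test occasions.** A13 gives pre, post, +24, +48, +72 and +168 h, which is 6 occasions. 6 × 2 parts = 12, which reproduces the count in A18. The count fits one soreness session per time point.

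**Step 2. Leg at each occasion under strict alternation.**

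| Occasion | pre | post | +24 h | +48 h | +72 h | +168 h |
|---|---|---|---|---|---|---|
| Leg | 1 | 2 | 1 | 2 | 1 | 2 |

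- Changes from baseline that cross legs: post, +48 h and +168 h, so 3 of 5.
- Successive changes that cross legs: 5 of 5.
- All pairwise time contrasts: 6 × 5 / 2 = 15, of which 3 × 3 = 9 cross legs.
- With the same leg, or both legs, at every occasion, 0 of 5 changes from baseline would compare different legs.

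**Step 3. Added noise.** With equal SDs, the variance of a change is 2σ²(1 − ρ). The ratio of cross-leg to same-leg variance is therefore (1 − ρ_cross)/(1 − ρ_same), and the loss of effective sample size for that change is 1 − 1/ratio. The protocol gives no correlations. The ranges here are assumptions.

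| ρ same leg | ρ across legs | Variance ratio | Loss |
|---|---|---|---|
| 0.8 | 0.8 | 0.2/0.2 = 1.0 | 0% |
| 0.8 | 0.7 | 0.3/0.2 = 1.5 | 33% |
| 0.8 | 0.6 | 0.4/0.2 = 2.0 | 50% |
| 0.9 | 0.8 | 0.2/0.1 = 2.0 | 50% |
| 0.9 | 0.7 | 0.3/0.1 = 3.0 | 67% |
| 0.9 | 0.6 | 0.4/0.1 = 4.0 | 75% |

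Over the assumed ranges the ratio runs from 1.0 to 4.0, a loss of 0 to 75% at the cross-leg times.

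**Step 4. Bias in a within-group paired t test.** Assume that everyone starts on the same leg, that there is no true change, that ρ across legs is 0.7 and that the mean leg difference is d in SD units. The SD of the change is √(2 × 0.3) = 0.775, and the noncentrality is d√n / 0.775. For n = 10 (one sex-by-load cell in Part A), the rejection rate of a two-sided 5% test is:

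| d | Noncentrality | Rejection rate |
|---|---|---|
| 0.1 | 0.41 | about 7% |
| 0.25 | 1.02 | about 15% |
| 0.5 | 2.04 | about 45% |

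The protocol gives no value for d. The table shows how the error would grow with d, not what it will be.

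**Step 5. Between-group contrasts.** The independent t tests in A62 compare the groups' readings at one time point. If both groups are on the same leg at that time, or have the same mix of legs, the leg effect cancels from the group difference and from group × time. If the mix differs, the difference is shifted by d times the difference in the proportions tested on each leg.

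**The case against.** The strongest point on the other side is that the reading is not settled. The rule stands only in the risk sections, and A13 names no leg, site or number of presses. The 12 in A18 counts sessions of algometry and VAS together, not presses, and 15 minutes per session leaves room for several. If both legs are pressed in turn at every session, the confounding disappears. This stands, so the point is conditional and its first request is for clarification. Sparing the same site still fits alternation between occasions more naturally.

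A second point is that both objectives in A10 are comparisons between groups. A reader might infer that the load, sex or protein comparisons are biased. The documents do not support that. Bias there needs a leg order that differs between groups, and the protocol neither says that it does nor ensures that it does not. The variance ratio for changes also does not carry over to tests that compare groups at a single time point.

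Third, a reader might infer a definite loss of precision, or that participants will in fact start on a habitual side. Neither is in the documents. The assumed correlations include the case of no loss.

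Fourth, a leg term and the starting leg could be left to an analysis plan or an operating procedure. That is fair for the model term alone. It does not cover the starting leg and the single pre-exercise test, which determine what data exist.

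Finally, the scope is narrow. The alternation rule is not applied to VAS soreness, blood markers or 1RM, the sample size in A60 rests on muscle strength, and the alternation has a sound reason.

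**Conclusion.** The point holds in a limited form. If legs alternate between occasions, 3 of 5 changes from baseline and every successive change in pain threshold compare different legs, and the planned paired t tests and ANOVA time effect take no account of it. That count follows from the schedule and needs no assumption beyond the reading of the rule.

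The consequences depend on quantities that the protocol does not give. Systematic error arises in the within-group time effects if participants tend to start on the same side and the legs differ on average. Added noise arises if the between-leg correlation is below the same-leg correlation, with a variance ratio of 1.0 to 4.0 under the assumed values. Only one outcome is touched. It is worth correcting because the remedy is cheap and has to be in place before data collection.

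**What to change.** State in A13 whether the test alternates between occasions or within each occasion. If both legs are pressed at every occasion, say so and define how the readings are combined; nothing further is then needed on this point.

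If it alternates between occasions:

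- Keep the alternation, so that the protection against bruising remains.
- Randomise the starting leg for each participant, balanced within group (within sex-by-load cell in Part A). Record the leg at each reading and include leg as a factor in the pain-threshold analysis. This alone removes the systematic confounding of leg with time.
- Preferably also take the pre-exercise reading on both legs, so that each later reading is compared with the same leg's own baseline. This deals with the added noise as well.

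The cost is one data column and one model term, plus one extra pain-threshold reading per participant at visit three if the two-leg baseline is adopted.
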